### Data collection

While the trial does not meet all criteria of a classic registry-based randomized controlled trial (e.g., registry-based randomization), it reflects key elements of the model by enabling efficient capture of rich, structured data through linkage with established registries. Both registries (BC Cardiac Arrest Registry and CARES) draw data from electronic ambulance call reports, fire service records, and hospital charts. They include patient demographics, timestamped prehospital interventions, and outcomes such as survival and neurological status at discharge. Both registries have employed robust data quality measures that have been reported elsewhere.^13^, ^15^ Operational data related to PulsePoint notifications are obtained directly from the PulsePoint server. For each randomized incident, data captured in the PulsePoint server include the date, time, and location of the event, randomization assignment, number and location of app users within the activation radius, and the proximity of the nearest registered public access AED. PulsePoint also provides jurisdiction-level metrics on mobile app uptake and penetration over time, including the number and geographic distribution of active app users. These data will be used to assess both the reach of the intervention and its implementation fidelity. De-identified data from the cardiac arrest registries, depending on case location, along with PulsePoint system data, are securely transferred to the study coordinating centre at Queen’s University. All data are stored in a dedicated REDCap (Vanderbilt University, Nashville, TN) instance hosted within the Centre for Advanced Computing at Queen’s University. The platform resides on secure, password-protected research server that adheres to recognized international standards for research data privacy and security, including physical and electronic safeguards consistent with ethical and legal requirements for health data management in both Canada and the United States. Data transferred and stored for the purposes of this study are de-identified and do not contain direct personal identifiers such as name, date of birth, or health card number. Each case is linked using a unique emergency service incident number, allowing case matching without the transfer of identifiable information into study databases.

### Safety

A comprehensive safety monitoring framework is embedded within the trial protocol. Adverse events and serious adverse events have been defined a priori, with specific criteria established to differentiate between events requiring clinical escalation and those involving scene dynamics or responder behavior. Examples of reportable serious adverse events include injury or death to a bystander, grossly negligent CPR resulting in harm, or violent altercations requiring medical intervention. Less severe but still reportable events include vandalism, property theft, non-injurious physical altercations, and scene overcrowding that impedes paramedic operations. Data sources for safety surveillance include structured abstraction from paramedic patient care records, quality improvement systems, and ongoing engagement with paramedic leadership. In addition, the trial employs routine safety check-ins at steering committee meetings and issues regular reminders to frontline personnel and data abstractors to facilitate early identification and documentation of any safety-related concerns.

### Analysis plan

The primary outcome will be compared between treatment groups using the Mantel-Haenszel Chi-square test, stratified by site. Estimates of the treatment effect will be reported as absolute risk differences and relative risks, each accompanied by 95 % confidence intervals. Binary secondary outcomes will be analyzed using the same stratified approach. Continuous outcomes, such as emergency services response time and on-scene time intervals, will be analyzed using the stratified Wilcoxon rank-sum (van Elteren) test to account for non-normal distributions while stratifying by site.

The secondary objective will be addressed using a hierarchical logistic regression model to examine factors associated with the receipt of bystander resuscitation following PulsePoint notification. This model will account for clustering by site and include independent variables such as age, sex, witnessed status, time of day, day of the week, paramedic response interval, number of PulsePoint users in proximity, and whether dispatcher-assisted CPR instructions were provided. Results will be expressed as adjusted odds ratios with 95 % Wald confidence intervals. The same modeling approach will be applied to selected binary secondary outcomes. Subgroup analyses will examine whether the effect of the intervention differs across key subpopulations. These will include a comparison of events in rural versus urban settings, as defined by Statistics Canada census metropolitan area classifications, and a comparison of cardiac arrests with witnessed shockable rhythms versus non-shockable rhythms. Interaction terms will be included in regression models to formally test for effect modification.

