### Sample size considerations

We calculated our target sample size to detect a 15 % absolute increase in bystander resuscitation attempts between treatment groups. The study steering committee determined this to be the minimal clinically important difference through consensus. Using updated simulations assuming a consistent odds ratio across strata with varying baseline event rates, we initially targeted a total sample size of 522 patients to achieve 90 % power, assuming a two-sided alpha of 0.05. However, partway through the trial, we revised the target sample size due to slower-than-anticipated recruitment, limited funding, and concerns about the feasibility of an extended study duration. To address these constraints, we reduced the target power to 80 %, yielding a revised sample size of 340 patients (170 per group). We did not account for missing patients in our revised calculations because recruitment data at the time indicated <1 % loss to follow-up.

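### The site-stratified primary test is valid, but it leaves unused plausibly prognostic baseline data already collected; prespecified adjustment would give a small to moderate, unquantified gain in power at N = 340

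*Protocol article*

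**What the plan says.** The Analysis plan section sets the primary test, "The primary outcome will be compared between treatment groups using the Mantel-Haenszel Chi-square test, stratified by site", and the effect measures: "Estimates of the treatment effect will be reported as absolute risk differences and relative risks, each accompanied by 95 % confidence intervals". Site is the only adjustment factor.

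The same section lists age, sex, witnessed status, time of day, day of the week, paramedic response interval, number of nearby PulsePoint users and dispatcher-assisted CPR instructions. They enter only a hierarchical logistic model for the secondary objective, which looks at factors associated with bystander resuscitation after notification and reports adjusted odds ratios. Under Data collection, the PulsePoint server captures for each randomised incident its date, time and location and the "number and location of app users within the activation radius". Demographics and event data come from the two registries.

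On size, the Sample size considerations section says: "We calculated our target sample size to detect a 15 % absolute increase in bystander resuscitation attempts between treatment groups". It continues that "we initially targeted a total sample size of 522 patients to achieve 90 % power, assuming a two-sided alpha of 0.05". The power target was then lowered to 80% and the total to 340 (170 per group), because of "slower-than-anticipated recruitment, limited funding, and concerns about the feasibility of an extended study duration".

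**The concern.** A trial that has given up power for want of patients has reason to use the information it already holds. Adjusting a randomised comparison for prognostic baseline variables usually narrows the interval. It also takes out of the estimate whatever chance imbalance in those variables remains. Site stratification alone does neither for age, sex, timing or the density of app users.

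The secondary model does not supply what is missing:

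- It is described as a study of factors following notification, not as an adjusted comparison of the two groups.
- It yields conditional odds ratios, which are a different quantity from the planned marginal risk difference and relative risk.
- It includes dispatcher instructions and paramedic response interval, both of which can fall after the alert. The response interval is itself listed as a safety outcome.

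The article therefore describes no baseline-adjusted risk difference or relative risk. At stake is some precision in the primary result.

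**Working it through.** **1. Inputs.** From Sample size considerations: a 15-point absolute difference, two-sided alpha 0.05, 522 patients at 90% power, then 340 at 80%. The figures came from simulations "assuming a consistent odds ratio across strata with varying baseline event rates". The control rate and stratum rates are not given, so a range is scanned. No odds ratio or R² is given for any covariate, so R² is assumed.

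**2. The plan's own figures.** With the usual pooled-variance formula, n per group = [1.960·√(2p̄(1−p̄)) + 0.842·√(p₁(1−p₁) + p₂(1−p₂))]² / 0.15².

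- 35% vs 50% and 50% vs 65% each give 169.3, rounded up to 170, so a total of 340. Control rates of about 31% to 54% come within 3% of 340. The figure is plausible, though it cannot be strictly reproduced without the control rate.
- At 90% power the largest total over all control rates is 464 (about 490 with continuity correction). Scaling directly, 340 × (3.242/2.802)² = 340 × 1.339 = 455. So 522 exceeds what the power change alone explains: 1 − 455/522 = 13%. This could reflect an allowance for missing patients or different stratum rates; the article does not say.

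**3. Power with adjustment, by formula.** Let R² be the share of outcome variance explained beyond site. Then power = Φ[(1.960 + 0.842)/√(1 − R²) − 1.960], and effective N = 340/(1 − R²).

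| Assumed R² | Power at N = 340 | Effective N |
|---|---|---|
| 0 | 80.0% | 340 |
| 0.02 | 80.8% | 347 |
| 0.05 | 82.0% | 358 |
| 0.10 | 84.0% | 378 |
| 0.15 | 86.0% | 400 |
| 0.20 | 87.9% | 425 |

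Returning to 90% needs R² = 1 − 1/1.339 = 0.25.

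**4. Power with adjustment, by simulation.** N = 340, two sites, four further baseline covariates, 4,000 replicates per setting. The site-stratified Mantel-Haenszel test was compared with a logistic model standardised to the risk difference (influence-function standard error).

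| Covariate strength (total R²) | 40% vs 55% | Gain over control rates 40% to 65% |
|---|---|---|
| Weak (0.02) | 80.5% to 80.8% | 0.3 to 0.7 points |
| Moderate (0.07) | 79.4% to 81.5% | 1.1 to 2.2 points |
| Strong (0.15) | 80.5% to 85.9% | 3.7 to 5.4 points |

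**5. Type I error.** Across the twelve null settings the adjusted test ran from 4.8% to 5.7% (Monte Carlo standard error about 0.3 points in each). The mean was 0.631/12 = 5.3%, against 0.589/12 = 4.9% for Mantel-Haenszel. Moving the level from 4.9% to 5.3% shifts the critical value from 1.968 to 1.938, which alone adds about 0.8 points near 80% power. The simulated gain in the weak setting cannot be told apart from this, and the other gains may be overstated by a similar amount.

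**The case against.** The strongest reply is that nothing here is wrong. Randomisation is stratified by site, the test is stratified by site, and the test supports the planned effect measures. The full analysis plan is not shown and may contain an adjusted supporting analysis. All of that stands. A reader might infer that the primary analysis is invalid or that adjustment is required; the documents support neither.

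Four further points also stand, and each limits the claim.

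- **Strength.** A reader might take witnessed status or user density to be strong predictors. The only relevant text is a qualitative remark in the Discussion that alerts tend to occur in dense areas where bystanders are more likely anyway. Restricting the cohort to public, paramedic-treated arrests with a responder within 400 m may also narrow the spread of the covariates.
- **Completeness.** Per-incident capture is stated only for the server data. The article gives no completeness figure for the registry variables.
- **Timing of witnessed status.** The British Columbia trigger codes include ineffective breathing and choking with altered consciousness. Such a patient could arrest after the call, and an alerted responder could then be the witness. In those cases witnessed status is not a baseline variable.
- **Balance.** Blocking within site never ensured balance on other covariates, and the confidence interval already allows for chance imbalance. If the worry is selective exclusion after randomisation, the Discussion acknowledges it, and adjusting for these covariates does not remove it.

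The remaining objection is lateness: 288 patients were in the primary dataset on 12 May 2025, with enrolment expected to finish by 1 December 2025. That is a cost, not a bar, because the Blinding section keeps the groups labelled A and B until the analysis is complete.

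**Conclusion.** The point holds as an efficiency improvement. The planned test is sound but leaves collected baseline information unused in a trial that has accepted lower power.

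Under an assumed R² of 0.02 to 0.15 beyond site, power at 340 goes from 80% to about 81% to 86%. The simulation agrees in direction in every setting, with gains from under 1 point to about 5. At the low end the benefit is negligible. A reader might infer that adjustment recovers the 10 points given up; that would need R² of about 0.25, and nothing in the documents suggests such a value.

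The conclusion rests on three assumptions: the R² range, an unstated control rate compatible with 340, and covariates that are nearly complete and truly fixed before the alert.

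**What to change.** Before unblinding, and before outcomes are tabulated by group label, prespecify as the primary estimate a logistic model with treatment, site, age, sex, time of day, day of week and number of app users within 400 m. Standardise it to the marginal risk difference and relative risk with robust 95% intervals. In addition:

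- Use the number of users within the radius, which the server records for every randomised incident, and not the number notified.
- Add witnessed status only where the collapse preceded the alert, or confine it to a sensitivity analysis.
- Exclude dispatcher CPR instructions, paramedic response interval and initial rhythm, which can arise after the alert.
- Fix the coding of each covariate, a rule for missing values, and a small-sample correction to the robust standard error in view of the slightly raised type I error above.
- Report the site-stratified Mantel-Haenszel result as a supporting analysis.

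No new data are needed. The cost is plan wording, some programming and a late but blinded protocol modification, which under Trial management must be reported to the site investigators, the monitoring board and the ethics boards. If that is judged too much at this stage, reporting the adjusted estimate as a prespecified supporting analysis would keep much of the information, but would not raise the power of the primary test.

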## Introduction

Out-of-hospital cardiac arrest (OHCA) is a time-critical emergency affecting approximately 60,000 Canadians and 356,000 Americans annually. Fewer than 10 % survive to hospital discharge.^1^, ^2^ Early cardiopulmonary resuscitation (CPR) and automated external defibrillator (AED) use can increase the odds of survival by two to three times,^3^, ^4^, ^5^, ^6^ but only if these interventions occur rapidly. The median paramedic response time is approximately seven minutes in optimized urban systems and can exceed 14 min in rural areas or hard-to-access urban locations.^7^, ^8^ To mitigate delays in professional response, efforts have been made to encourage bystander CPR and AED use while professionals are en route. Despite sustained global efforts to promote CPR and public access defibrillation, bystander CPR occurs in fewer than 50 % of OHCA cases, and bystander AED use remains below 3 % in many communities.^2^

Community volunteer responder programs using mobile apps, text messages, or other dispatch technologies have emerged as promising strategies to reduce delay to CPR and defibrillation. However, the International Liaison Committee on Resuscitation (ILCOR) has classified the evidence supporting community first responders engaged by technology as “very low-certainty” and has called for clinical trials to generate more robust evidence.^9^ The only published randomized controlled trial (RCT) to date was done in Scandinavia,^10^ highlighting the need for replication in other geographical contexts.

To address the evidence gap, we have designed and implemented a RCT to evaluate the impact of a commonly used mobile device application called “PulsePoint Respond” designed to crowdsource bystander resuscitation for patients who experience OHCA. Our primary objective is to determine whether “CPR Needed” alerts sent via the PulsePoint Respond app during dispatch procedures increase the occurrence of bystander CPR or AED use before professional responders arrive, compared with standard dispatch procedures without PulsePoint alerts. Our secondary objective is to examine how cardiac arrest event characteristics (e.g., initial rhythm, location type, time of day) and system characteristics (e.g., PulsePoint user density) influence the likelihood of bystander resuscitation following a PulsePoint alert.

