### Automated patient recruitment and randomization

Inclusion criteria for the study are 1) 9-1-1 calls assigned as “suspected” or “confirmed” OHCA, and 2) OHCA confirmed as paramedic-treated, public location OHCA. Exclusion criteria include 1) a traumatic cause of cardiac arrest, 2) cardiac arrest occurring in the context of a dangerous scene as determined by the 9-1-1 call-taker, 3) paramedic-witnessed cardiac arrest, 4) cardiac arrest not treated by paramedics (Do Not Resuscitate or signs of obvious death), 5) cardiac arrest occurring in nursing homes. To operationalize these criteria and facilitate the recruitment of OHCA patients at the time of the 9-1-1 call, we undertake the following processes. All 9-1-1 calls coded as possible OHCA incidents occurring in non-residential locations in the computer-assisted dispatch systems of participating communities are automatically enrolled into the trial and undergo random allocation to a treatment group by the PulsePoint server. In BC, Medical Priority Dispatch System codes 09D01 (ineffective breathing), 09E01 (respiratory arrest), 09E02 (uncertain breathing status), 11D01 (choking with altered level of consciousness), 11D02 (choking with abnormal breathing), 11E01 (verified choking), 12D01 (convulsions with absent breathing), and 14D01 (unconscious drowning) define possible OHCA. In Columbus, Association of Public-Safety Communications Officials (APCO) call designators “Cardiac Arrest”, and “Drowning” are used. When the trial was launched, Columbus had also included “Unconscious Overdose”, and “Unconscious Person”, but these codes were later removed from our randomization trigger criteria due to very low specificity for OHCA. Random allocation occurs using code embedded within the PulsePoint server activation process for “CPR Needed” alerts. The code references a randomization table generated by the study statistician enabling 1:1 random allocation, stratified by site, using permuted blocks of varying sizes. For each eligible 9-1-1 call, the next entry in the randomization table determines group assignment. If allocated to the treatment group, the PulsePoint activation proceeds as designed. If assigned to the control group, the process stops before any “CPR Needed” notifications are sent. Each allocation is automatically logged by the server and used by study staff to track enrollment.

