### Primary analysis eligibility and case confirmation

Randomized patients will be considered eligible for the primary analysis only if they satisfy inclusion criteria, meet no exclusion criteria, and also have at least one PulsePoint responder within 400 m at the time of the 9-1-1 call. Because the intervention and its intended effect must occur before paramedic arrival, randomization must also occur before patient eligibility for the primary analysis can be determined. Study staff retrospectively review each randomized case to determine whether it meets criteria for inclusion in the primary analysis. This approach allows rapid randomization but will introduce many post-randomization exclusions (Fig. 2).

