## Discussion

Crowdsourcing applications like PulsePoint Respond, which alert nearby lay responders to suspected cardiac arrests, offer a novel approach to improving early resuscitation. While observational studies and system-level evaluations suggest possible benefits^16^, ^17^, ^18^, ^19^, ^20^, ^21^, ^22^, ^23^, ^24^, ^25^, ^26^, ^27^, ^28^, ^29^, ^30^, evidence from randomized trials remains limited. Only one published RCT has evaluated crowdsourcing technology for OHCA, but it involved a text-message based intervention in a Scandinavian setting, included private residential locations, was only active during the daytime, and did not involve notification of nearby public AED locations.^10^ The benefit observed in this trial was encouraging, but modest. The intervention increased bystander CPR by 13.9 percentage points without any significant increase in survival.

Despite the paucity of data from clinical trials, this approach has proliferated. We conducted a scoping review of the literature which identified an 25 different crowdsourcing technologies being used in 15 countries around the globe.^31^ At the time of writing, PulsePoint has been implemented in over 5300 U.S. communities and has more than 1.3 million app users.^32^ This widespread adoption without more evidence from clinical trials is problematic. Observational studies such as pre-post comparisons or analyses of alerted vs. non-alerted cases, are prone to significant bias. Bystander CPR rates could increase over time due to unrelated public health initiatives, and alerts tend to occur in densely populated areas where circumstantial bystanders are more likely regardless of the app. These factors could result in an overestimate of the true impact of the technology.

In this context, clinical equipoise remains due to uncertain benefit, associated costs, and potential risks of crowdsourcing technology. Agencies adopting the technology incur expenses related to software licensing and the human resources required for program management, and ongoing public engagement. Theoretical risks include potential injuries to responders en route, liability issues for hosting agencies, unsafe scene conditions for responders, and risks to patient safety through poor-quality CPR, privacy breaches, and theft. These uncertainties underscore the need for high-quality evidence from clinical trials to determine whether the benefits of crowdsourcing technologies for OHCA justify their costs and potential risks.

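### The model for the secondary objective appears to cover notified cases only, so its user-density coefficient cannot show how density influences the response to an alert

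*Protocol article*

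**What the plan says.** The Introduction sets the secondary objective: to examine how event characteristics (initial rhythm, location type and time of day are the examples) and system characteristics (PulsePoint user density is the example) "influence the likelihood of bystander resuscitation following a PulsePoint alert".

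The Analysis plan assigns this objective a "hierarchical logistic regression model to examine factors associated with the receipt of bystander resuscitation following PulsePoint notification". The model accounts for clustering by site. Its covariates are introduced as examples: age, sex, witnessed status, time of day, day of week, paramedic response interval, "number of PulsePoint users in proximity, and whether dispatcher-assisted CPR instructions were provided". Neither randomised group nor any group-by-factor term is listed, and no analysis set is named. The same approach is to be used for selected binary secondary outcomes.

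The section on recruitment and randomization says of controls: "If assigned to the control group, the process stops before any" alert goes out.

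The Analysis plan then describes separate subgroup analyses of whether the intervention effect differs, with formal interaction terms. It names two: rural versus urban, and witnessed shockable versus non-shockable rhythm.

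On available data, the server captures "randomization assignment, number and location of app users within the activation radius" for each randomized incident (Data collection). To enter the primary analysis a case in either arm must "have at least one PulsePoint responder within" 400 m (Primary analysis eligibility and case confirmation).

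**The concern.** Places with many app users are likely to be places with many people, and so with more chance bystanders. In a model confined to alerted cases, a positive density coefficient can arise because more users were alerted, because more people were there anyway, or both. Nothing in the alerted arm separates the two. The listed covariates do not measure background bystander presence directly, witnessed status being at best a partial proxy, so adjustment is unlikely to remove it.

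The Discussion recognises this mechanism when it warns that "alerts tend to occur in densely populated areas where circumstantial bystanders are more likely regardless of the app".

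The trial is meant to guide policy on app-based responders, and low app uptake is described as a main obstacle to recruitment. An odds ratio for nearby users, reported under an objective worded as influence, could be taken as evidence that more downloads make the alert work better, even if the alert had no effect.

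**Working it through.** The plan states no figure to reproduce here, so the check is in two parts.

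**1. Which cases the model covers.** The model concerns resuscitation after notification, and controls receive no notification. Together these leave alerted cases only. This is an inference, though the natural one. Density is recorded for every randomised incident and is defined for controls, so a model in both arms is feasible with existing data.

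**2. What each model estimates.** Let x be user density in SD units and t the randomised group (1 = alert):

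logit P(resuscitation) = a + b·x + t·(d + m·x)

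Here b is the background association, d the alert effect at mean density and m the change in the alert effect per SD.

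- Alerted-only slope for density: b + m.
- Control-arm slope: b.
- Group-by-density interaction in both arms: (b + m) − b = m.

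Only the last isolates how density changes what the alert does.

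**Inputs.** From the Sample size section: 170 per group, two-sided 0.05. Assumed, because the documents do not give them: a 50% control rate at mean density; background odds ratio exp(b) of 1, 1.25, 1.5 or 2 per SD; density normally distributed; no other covariates. The alert effect d is either 0 or 0.60 on the logit scale, which moves 50% to 1/(1 + e^−0.60) = 65%, the plan's 15-point difference. There were 1,500 simulated trials per scenario.

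**No modification by density (m = 0):**

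| Background OR per SD | Alert effect d | Alerted-only OR | Alerted-only p<0.05 | Interaction OR | Interaction p<0.05 |
|---|---|---|---|---|---|
| 1 | 0 | 1.00 | 5.2% | 1.00 | 4.7% |
| 1.25 | 0 | 1.25 | 29.5% | 0.99 | 5.7% |
| 1.25 | 0.60 | 1.26 | 27.1% | 1.00 | 6.1% |
| 1.5 | 0 | 1.52 | 71.7% | 1.00 | 5.7% |
| 1.5 | 0.60 | 1.53 | 69.3% | 1.01 | 4.5% |
| 2 | 0 | 2.03 | 98.6% | 1.00 | 5.2% |
| 2 | 0.60 | 2.02 | 98.5% | 1.00 | 4.7% |

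The alerted-only model returns the background odds ratio whether or not the alert works. The interaction stays near 1. Its rejection rates are compatible with 5%, since the Monte Carlo error is √(0.05 × 0.95/1500) = 0.6 points.

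**Hand check.** With 170 alerted cases at 50%, SE(b) ≈ 1/√(170 × 0.25) = 0.153. For an odds ratio of 1.5, ln 1.5/0.153 = 0.405/0.153 = 2.64, and Φ(2.64 − 1.96) ≈ 0.75, close to the simulated 0.72.

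**True modification (interaction OR 1.5 per SD, d = 0.60):**

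| Background OR | Alerted-only OR | Interaction OR | Interaction power |
|---|---|---|---|
| 1 | 1.51 | 1.51 | 41% |
| 1.25 | 1.91 | 1.52 | 39% |
| 1.5 | 2.29 | 1.50 | 35% |
| 2 | 3.08 | 1.51 | 30% |

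The alerted-only odds ratio is roughly the product of the two (1.5 × 1.5 = 2.25 against 2.29). The interaction recovers 1.5, but with low power.

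**The case against.** The strongest reply is that the model answers the question as put. The objective speaks of resuscitation after an alert and the model of factors associated with it. That is a prognostic question among alerted cases, and effect modification is handled separately. This stands in part: as a description of alerted cases the model is valid. It does not meet the word influence in the objective, nor an interest in user density as something that could be changed.

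Three stronger readings are tempting, and the documents do not support them.

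- A reader might infer that the randomised control arm goes unused. It does not: the subgroup analyses compare arms with interaction terms, and one partly covers initial rhythm, an example in the objective. What can be said is that user density, time of day and location type are not named there, although that list is not stated to be complete.
- A reader might infer that the Discussion condemns this very model. Its criticism is of pre-post comparisons and of alerted versus non-alerted cases as estimates of the technology's impact. The mechanism carries over, but the article does not say so of predictor models.
- A reader might take the simulated 27% to 99% as false-positive rates. For a question about association they are not: a real background association was put in and detected. They mislead only if the coefficient is read as an effect of the alert, and the article never says that it will be.

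The article is also a condensation. The covariate list is open and the analysis set unnamed, so the full protocol and analysis plan may settle both.

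**Conclusion.** The point holds in a limited form. As described, the model for the secondary objective appears confined to notified cases, and its density coefficient combines background bystander presence with any effect through the alert. It cannot show how density influences the response to an alert. That the two components add on the logit scale is algebra and needs no assumed figure. How large the background part is depends on the density-to-bystander association, which the documents do not give; the 1.25 to 2 per SD used here is an assumed range, and the simulation had no covariate adjustment. The primary comparison is unaffected. This is worth correcting because it costs only analysis wording and the data exist in both arms.

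**What to change.** In the primary analysis set, fit the model in both arms with site, randomised group, the listed factors and a group-by-factor interaction. The first interaction should be for the number of app users within 400 m; time of day and location type can follow if wanted. Report the alert effect at set levels of the factor, and base any statement about influence on the alert's effect on the interaction. The paramedic response interval is complete only after allocation, and the dispatcher instructions may also come after it, so show the interactions with and without these two covariates. Label the interactions exploratory. Keep an alerted-only model if useful, but call it descriptive and state that its odds ratios include background bystander presence.

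No new data are needed. The cost is precision: with 340 patients, power is only about 30% to 41% for an interaction odds ratio of 1.5 per SD, so intervals will be wide and the result may be inconclusive. The report should say so in advance.
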